## Abstract

**Introduction:**

Mental healthcare organisation can either pursue *specialisation*, that is, distinct clinicians and teams for inpatient and outpatient care or *personal continuity of care*, that is, the same primary clinician for a patient across the two settings. Little systematic research has compared these approaches. Existing studies subject have serious methodological shortcomings. Yet, costly reorganisations of services have been carried out in different European countries, inconsistently aiming to achieve specialisation or personal continuity of care. More reliable evidence is required on whether specialisation or continuity of care is more effective and cost-effective, and whether this varies for different patient groups and contexts.

**Design and methods:**

In a natural experiment, we aim to recruit at least 6000 patients consecutively admitted to inpatient psychiatric care in Belgium, Germany, Italy, Poland, and the UK. In each country, care approaches supporting specialisation and personal continuity coexist. Patients will be followed up at 1 year to compare outcomes, costs and experiences. Inclusion criteria are: 18 years of age or older; clinical diagnosis of psychosis, affective disorder or anxiety/somatisation disorder; sufficient command of the language of the host country; absence of cognitive deterioration and/or organic brain disorders; and capacity to provide informed consent.

**Ethics and dissemination:**

Ethical approval was obtained in all countries: (1) England: NRES Committee North East—Newcastle & North Tyneside (ref: 14/NE/1017); (2) Belgium: Comité d'Ethique hospitalo-facultaire des Cliniques St-Luc; (3) Germany: Ethical Board, Technische Universität Dresden; (4) Italy: Comitati Etici per la sperimentazione clinica (CESC) delle provincie di Verona, Rovigo, Vicenza, Treviso, Padova; (5) Poland: Komisja Bioetyczna przy Instytucie Psychiatrii i Neurologii w Warszawie. We will disseminate the findings through scientific publications and a study-specific website. At the end of the study, we will develop recommendations for policy decision-making, and organise national and international workshops with stakeholders.

**Trial registration number:**

ISRCTN registry: ISRCTN40256812.

Strengths and limitations of this studyThis study will be the largest one comparing care approaches based on specialisation and personal continuity of care worldwide.It will involve services across five European countries and comprehensively assess outcomes, costs and experiences of the ‘specialisation’ and ‘personal continuity’ care approaches.The natural experiment methodology has the advantage of allowing comparisons of the two approaches without altering already established routine provision of care.Being a natural experiment, patients will not be randomised to either approach. Clustering in outcomes may be found within hospitals and countries. We will explore random effects for hospitals using mixed regression models.Selection bias at baseline and attrition at follow-up are common pitfalls in large prospective studies on people with severe mental disorders. We will attempt to: (1) minimise selection bias through approaching all patients within a few days from a hospital admission; and (2) reduce attrition using medical records or brief phone interviews to collect the main outcome data.

## Introduction

A central question in mental healthcare is whether to prioritise specialisation of clinicians and clinical teams or personal continuity of care.^1–4^ These two care approaches are sometimes incompatible as each one requires a different organisation of care.^1^
^5^

Following the specialisation approach, mental healthcare should be provided by different clinicians and teams in inpatient and outpatient settings. This care approach is expected to simplify the practical organisation of services; support quick clinical decision-making; enable clinical teams and clinicians to have a full focus on only one setting; and foster an expertise in setting specific aspects of treatment.^1^
^6^

According to the personal continuity of care approach, however, the same primary clinician is responsible for a given patient within both inpatient and outpatient settings. This approach may facilitate the smooth transition of patients from one setting to another; support long-lasting therapeutic relationships; and simplify clinical communication as patients and clinicians are familiar with each other across the care settings.^2^
^3^
^7^

The expected benefits of specialisation and personal continuity of care are summarised in table 1.

**Table 1 BMJOPEN2015008996TB1:** Expected benefits of specialisation and personal continuity of care

Areas	Specialisation	Personal continuity of care
Organisational aspects at a service level	Quick clinical decision-making; positive risk management	No fragmentation of services; increased engagement with patients who are less likely to actively seek treatment
Clinical benefits	Specialisation of interventions	Continuity of care
Impact on routine care	Enhancement of clinical leadership and specialised expertise	Establishment of a stronger therapeutic relationship

Yet, solid evidence on which of these two approaches is associated with better outcomes is lacking. As a consequence, service reorganisations are inconsistent across Europe and the issue repeatedly raises debate.^3^
^8–10^

In the UK, although the organisation of mental healthcare traditionally favoured personal continuity of care,^3^
^7^ most provider organisations of mental healthcare (ie, NHS Trusts) have now established specialised hospital and community teams.^5^
^11^
^12^

In Germany, the traditional approach has been characterised by specialisation of clinicians and teams, while recent initiatives (‘Integrierte Versorgung’, ie, ‘Integrated healthcare’) have aimed to strengthen continuity of care and to make one service responsible for both inpatient and outpatient care.^2^
^4^

In various other European countries (eg, Austria, Belgium, Denmark, France, Italy, Netherlands, Norway, Poland, Sweden, Switzerland) similar experimental programmes and professional debates are currently ongoing to change traditional mental healthcare approaches^13–20^ (see figure 1).

**Figure 1 BMJOPEN2015008996F1:**
[figure not shown]
National reforms and changes in mental healthcare organisation.

A systematic review comparing approaches based on specialisation or personal continuity of care found there was a general tendency towards better outcomes and patient/clinician preferences for approaches prioritising personal continuity of care.^21^ However, most studies had serious methodological shortcomings and definitive conclusions could not be drawn.

The studies included in the review shared the following limitations:^21^
They were conducted in local settings.Their samples were not large enough to detect small differences in outcomes between care approaches. Yet, small differences, for example a reduction of 5% in the number of re-hospitalisations, may have a significant impact on a national scale.The studies have assessed only a limited range of outcomes, disregarding outcomes like patient safety and cost-effectiveness.All the studies compared a newly implemented care approach (either favouring specialisation, eg, in the UK or personal continuity of care, eg, in Germany) with the traditional approach. With the exception of patient experiences and preferences, which were consistently in favour of care approaches supporting personal continuity of care,^5^
^22^ other outcomes were always positive for the new experimental approach irrespective of the type (‘novelty bias’).^21^

To address the limitations of the available studies, we have designed a natural experiment comparing approaches favouring either specialisation or personal continuity of care in five European countries (Belgium, Germany, Italy, Poland and UK). In all these countries, both approaches to care exist within routine practice.

Mental healthcare approaches were categorised based on whether a patient has the same ‘primary clinician’ for their inpatient and outpatient care or not. The ‘primary clinician’ is the clinician who is primarily responsible for the patient (usually a psychiatrist or a psychologist). The two approaches were operationalised as follows:
‘Specialisation approaches’ are those in which different primary clinicians are responsible for the treatment of a patient, depending on whether the patient is in the inpatient or outpatient care.‘Personal continuity approaches’ are those in which the same primary clinician is responsible for both inpatient and outpatient care of a patient.

This study was funded by the 7th Framework Programme of the European Commission (Full title: Comparing policy, framework, structure, effectiveness and cost-effectiveness of functional and integrated systems of mental health care—COFI).

COFI will be the largest study comparing specialisation and personal continuity of care, reaching more patients than all of the previous studies combined. The study will involve a comprehensive assessment of outcomes, cost-effectiveness and patient/clinician experiences. It will include services in which specialisation or personal continuity approaches are the standard way of providing mental healthcare, rather than experimental programmes.

The comparison of the two approaches will be carried out in a wide range of settings, and in countries with different traditions and practices of mental healthcare. ‘Specialisation’ and ‘personal continuity’ approaches are supported in these different countries by a variety of funding mechanisms, policies and clinical arrangements. This will allow for the generalisability of our findings from the participating countries to a higher number of countries with similar characteristics.

## Aims and objectives

COFI aims to compare outcomes, costs and experiences of ‘specialisation’ and ‘personal continuity’ of care approaches.

Readmission to hospital was chosen as the primary outcome of the study due to the high clinical relevance and impact on service costs. The validity of readmission rates as an outcome criterion for mental health service evaluation has been confirmed in previous studies.^23^
^24^

COFI will address the following research questions:
Primary research question
Do rates of rehospitalisation differ between the specialisation and personal continuity approaches?Clinical and social outcomes
Is there a difference in number of voluntary and compulsory rehospitalisations per patient and yearly inpatient bed days between the two approaches?Are untoward incidents (deaths, suicides, physical violence committed or experienced by patients) more frequent in either approach?What are the social outcomes, in terms of employment, accommodation, living situation, subjective quality of life and social contacts of patients treated by either approach?Costs of care:
What are the direct costs of care (ie, related to use of services) within each approach?Which approach is most cost-effective?Experience of care
What are treatment satisfaction and experiences of care provided by the two approaches and do they differ?

We will also carry out comparisons of the two approaches in subgroups of patients defined by age, gender, diagnosis, first admission, socioeconomic situation, migrant status and presence of physical comorbidities.

We hypothesise that:
The ‘specialisation approach’ may be more effective in providing specialised care for people with less complex and more specific mental health needs (eg, absence of comorbid disorders or social problems), who do not require coordination of different interventions.^1^
^12^The ‘personal continuity approach’, ensuring a stronger coordination of different interventions,^7^
^25^ may be more suited for treating patients who are affected by severely disabling mental health conditions (eg, schizophrenia) and comorbid physical illnesses, or those who have complex psychosocial needs such as patients with a low socioeconomic status, migrants and patients with comorbidities.

## Design and methods

### Study design

COFI is a natural experiment, prospectively following up for 1 year patients who, at the point of entry in the study, are hospitalised within care services adopting either a ‘specialisation’ or ‘personal continuity’ approach. Participating sites are located in five countries (Belgium, Germany, Italy, Poland and UK). In these countries both approaches are present, although practice, traditions, policies and funding of mental healthcare vary significantly.

Each included patient can only be treated within either a ‘specialisation’ or ‘personal continuity’ care approach, and the exposure of patients to either approach is outside of the control of investigators and hence, naturalistic. Allocation to either model is based on the given organisation of care in a defined geographical area (UK, Italy), on a clinical decision and patients’ choice (Belgium, Poland), or on insurance arrangements (Germany).

The methodology of a natural experiment has the main advantage of allowing comparisons of the two approaches without altering already established routine provision of care.

However, this implies that no randomised allocation of patients to different approaches is possible. Given the risk of bias associated with a non-randomised design, adjustment for potential confounders is of paramount importance.^26^ In our study, potential confounders will be adjusted for by exploring random effects at a hospital level which will provide an estimate of the potential variability of practice and outcomes both within countries and in different services within the countries.

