### Baseline measures

At baseline, we will collect data on:
Sociodemographic characteristics: year of birth, gender, marital status, highest completed education level, country of birth;Social situation: employment, accommodation, living situation, friendships, self-reported benefits receipt due to low income;Psychiatric and non-psychiatric diagnoses according to the International Classification of Disease 10 (ICD-10);^27^ the primary clinical diagnosis is established from medical records or clinician’s report at discharge from hospital;Severity of illness, rated by treating psychiatrists by the Clinical Global Impression Scale (CGI);^28^Whether the current admission is the first one or not;Formal status at admission (involuntary/voluntary);Patient appraisal of inpatient care, as measured by the Client Assessment of Treatment (CAT).^29^

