### Procedures

#### Establishing exposure to ‘specialisation’ or ‘continuity’ of care approach

To reflect differences in how mental healthcare services operate in the five countries, different procedures are used to ascertain exposure status to either a ‘specialisation’ or ‘personal continuity’ of care approach.

In the UK and in Italy, all patients admitted to the same hospital are treated under the same care approach, either a ‘specialisation’ or ‘personal continuity’ approach. In these countries, the local providers of care, that is, an ‘NHS Trust’ in UK and a ‘Dipartimento di salute mentale’ in Italy, may follow either the ‘specialisation’ or ‘personal continuity’ of care approach. The care is organised in the same way for all patients treated by the same provider of care which operates in a specific geographic area.

In Belgium, Germany and Poland, patients admitted to the same hospital can be treated under either a ‘specialisation’ or a ‘personal continuity’ of care approach. This is determined by patients’ health insurance arrangements (Germany) and/or by a mental health team decision in which the patient may or may not be involved (Belgium, Poland and Germany). Therefore, a patient is included in either group based on the primary hospital clinician report at discharge in Belgium, Poland and Germany.

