## Data analysis plan

### Adjustment for confounders

The coexistence of the two care approaches in the five participating countries may be considered a major strength of the present study. Yet, clustering in outcomes may be found within hospitals and countries; therefore, we will explore random effects for hospitals as part of mixed regression models.

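### The article credits hospital random effects with adjusting for confounding, which they do not do, and the fixed-effect list that does the adjusting omits benefits receipt, migrant status and comorbidity

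*Protocol article*

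**What the plan says.** Study design sets the standard: "Given the risk of bias associated with a non-randomised design, adjustment for potential confounders is of paramount importance". It then names the means: "potential confounders will be adjusted for by exploring random effects at a hospital level". The rest of that sentence describes estimating variability of practice and outcomes, which is what random effects do. The section Adjustment for confounders mentions clustering within hospitals and countries and concludes "therefore, we will explore random effects for hospitals as part of mixed regression models". It lists no covariates.

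Analysis of clinical and social outcomes gives the actual model. It is a mixed model with a random effect for hospital or, in Germany, Belgium and Poland, for the care-approach cluster within hospital. The fixed effects are age, gender, diagnostic group, previous admission, baseline severity, SIX score and formal status. Low-income benefits, migrant status and comorbidity (substance use, diabetes, cardiovascular disease) appear in the same section only as exploratory subgroup factors, entered as interactions.

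On allocation, the article says that UK and Italian patients receive whichever approach their area's provider uses. In Belgium, Poland and Germany both approaches can occur in one hospital. There the group follows from insurance (Germany) and/or is set "by a mental health team decision in which the patient may or may not be involved"; Study design adds patients' choice for Belgium and Poland. Aims and objectives expects personal continuity to suit patients with severely disabling conditions, physical illness or complex psychosocial needs, "such as patients with a low socioeconomic status, migrants and patients with comorbidities".

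**The concern.** The two places where a reader looks for the handling of confounding give a method that cannot handle it. A random intercept describes residual correlation among patients in the same unit, and the model assumes that it is independent of exposure. Where the approach is constant within the unit, the intercept cannot separate approach from the patient mix that came with it. This is so for hospitals in the UK and Italy, and for approach clusters within hospitals in the other three countries. Where both approaches share one hospital intercept, patient-level selection inside the hospital remains.

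The covariate list therefore carries the whole burden. It lacks three characteristics that the article itself treats as relevant to which approach suits a patient, in a design where three of the five countries allocate patient by patient. If teams, patients or insurers sort on these characteristics, and the characteristics also predict readmission, the primary comparison is biased. The study looks for a 5-point difference and intends policy recommendations, so a bias of a few points would matter.

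**Working it through.** **1. The plan's own figures.** Inputs from Sample size determination: 27.5% v 32.5%, 80% power, 5% significance (taken as two-sided), m = 128, ICC = 0.007.

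- Per group: [1.96√(2×0.30×0.70) + 0.8416√(0.275×0.725 + 0.325×0.675)]² / 0.05² ≈ 1317.4, rounded up to 1318, or 2636 in total. With continuity correction the total is 2716, as stated.
- Design effect: 1 + 127×0.007 = 1.889. Then 2716×1.889 = 5131 and 2716×1.90 = 5160, against the stated 5162.

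The sample size reproduces and is not in dispute.

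**2. Which variables are collected, and which are adjusted for.**

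| Characteristic linked to an approach in Aims and objectives | Baseline source | Primary fixed effect? |
|---|---|---|
| Severe condition, e.g. schizophrenia | diagnosis, CGI | yes (diagnostic group, severity) |
| Low socioeconomic status | SIX items; benefits receipt | in part (SIX); benefits no |
| Migrant status | country of birth ("marital status, highest completed education level, country of birth") | no |
| Physical or other comorbidity | psychiatric and non-psychiatric diagnoses | no |

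**3. Size of bias from one omitted factor.** Bias in the risk difference = (readmission risk difference of the factor) × (its prevalence difference between approaches). The documents give neither input, so both are assumptions.

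| Factor's risk difference | Imbalance 5 points | 10 points | 20 points |
|---|---|---|---|
| 10 points | 0.5 | 1.0 | 2.0 |
| 15 points | 0.75 | 1.5 | 3.0 |
| 20 points | 1.0 | 2.0 | 4.0 |

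The range is 0.5 to 4 points, or 10% to 80% of the 5-point target. It does not allow for the seven planned covariates.

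**4. Does the random intercept remove any of it?** Simulation: 40 hospitals × 128 patients, ICC 0.007, true effect zero, one omitted binary factor (mean prevalence 30%, risk difference 15 points, imbalance 20 points), linear random-intercept models, 150 replicates. Expected bias is 0.15×0.20 = 3.0 points. Mean estimates in points:

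| Structure | Crude | Random intercept | Random intercept + factor as fixed effect | Monte Carlo SE |
|---|---|---|---|---|
| Approach constant within hospital (UK, Italy) | 3.02 | 3.02 | 0.03 | 0.16 |
| Random effect for approach cluster within hospital | 2.92 | 2.92 | -0.08 | 0.13 |
| Both approaches under one hospital intercept | 3.17 | 3.17 | 0.14 | 0.10 |

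The random intercept removes none of the bias. The fixed effect removes it to within simulation error.

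**5. Consequence for the test.** SE at the planned size = √(2×0.30×0.70 / (5162/1.889/2)) = 1.75 points. False-positive rate at bias b = 1 − Φ(1.96 − b/SE) + Φ(−1.96 − b/SE). For b = 0.5, 1, 2 and 3 points this gives 5.9%, 8.8%, 20.7% and 40.2%.

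**The case against.** The strongest reply is that the plan does adjust for confounding. Seven baseline fixed effects include severity, diagnosis, admission history and formal status, and Potential challenges again refers to fixed effects of patient-level variables. SIX covers employment, accommodation, living situation and friends, so part of socioeconomic position is captured. This stands. It would be wrong to infer that confounding is left to random effects alone; Study design and Adjustment for confounders misdescribe a better plan.

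Second, saying that an approach suits certain patients is a statement about effect modification, which the planned interactions address. It does not show that those patients are allocated differently. This also stands: the concern arises only from combining it with patient-level allocation in three countries. In the UK and Italy allocation is geographical, so sorting by a clinical team does not arise there.

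Third, the simulation tests a random intercept with and without one omitted factor, not the planned model with its seven covariates. Those may shrink both the imbalance and the risk difference.

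Three stronger readings are tempting but unsupported:

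- **Education and marital status should be added too.** Both are collected, but Aims and objectives links neither to an approach and neither is a subgroup factor.
- **The bias could equal the 5-point target.** The assumed ranges stop at 4 points per factor. Passing 5 needs a wider assumption, such as a 30-point imbalance with a 20-point risk difference (6.0 points).
- **Hospital fixed effects are required in Belgium, Germany and Poland.** They would confine the estimate to within-hospital contrasts, which is where selection by indication is suspected, so they are a debatable trade-off.

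**Conclusion.** The point holds in two parts. The statement that hospital random effects adjust for confounders is wrong, and it conflicts with the model given later in the same article. The primary covariate list omits benefits receipt, migrant status and physical or substance-use comorbidity. These are available at baseline and may be related to allocation where the approach is set per patient.

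The size of the residual bias is unknown. The 0.5-4 points per factor rests on assumed imbalances of 5-20 points and risk differences of 10-20 points, before allowing for the seven planned covariates. The false-positive rates are illustrative in the same sense. What does not depend on these assumptions is that a random intercept does not remove patient-level confounding. This concerns what the article states, so it is not a detail left to an analysis plan that is not shown.

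**What to change.** 1. Reword Study design and Adjustment for confounders to say that confounding is addressed by measured baseline covariates and that random effects handle clustering only.
2. Add three fixed effects to the primary model, using the article's own subgroup definitions: low-income benefits receipt, country of birth different from country of residence, and comorbidity (substance use, diabetes, cardiovascular disease).
3. As a sensitivity analysis, show the estimate for the area-allocated countries (UK, Italy) and for the patient-level-allocated countries (Belgium, Germany, Poland) beside the pooled result.

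The cost is wording, a few extra parameters, which about 6000 patients support easily, and some missing covariate data to handle. No new data collection is needed. Residual confounding should still be acknowledged: insurance, which drives allocation in Germany, is not among the baseline measures the article lists, and these additions do not address it.
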